#### Primary outcome measure

2.6.1

##### FDI

2.6.1.1

The FDI, which consists of ten questions including five questions regarding physical function and five questions regarding social function and well-being, is a self-reported questionnaire for assessment of disability in patients with facial nerve disorder. The FDI score will be measured at a pre-trial screening and at weeks 0 (baseline), 4, and 8 (primary end point). The change from baseline at 8 weeks will be compared between the groups as the primary outcome.

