### Participants

2.2

Individuals of both sexes fulfilling the following inclusion criteria will be included in this study:

(1)age 18–65 years(2)a diagnosis of Bell's palsy made ≥3 months prior to screening(3)Facial Disability Index (FDI) <80 on the social aspect and <70 on the physical aspect(4)ability to communicate adequately with the researcher and respond to the questionnaire in writing(5)willingness to sign a form stating that they will not receive any treatment other than the prescribed treatment within the treatment period, and(6)willingness to participate in the study after providing written informed consent.

Participants with the following characteristics will be excluded:

(1)a history of receiving any other treatment that may affect the study outcomes for 2 months prior to the screening (oral administration of steroids or antiviral drugs, surgical history for treatment of facial palsy such as facial nerve compression, or facial TEA);(2)history of hypersensitivity to TEA or severe keloid;(3)Ramsay-Hunt syndrome;(4)bilateral facial nerve palsy or recurrent facial nerve palsy (more than two occurrences);(5)secondary facial nerve palsy from multiple neuritis, tumor invading the temporal bone, trauma, brain contusion, or stroke;(6)chronic otitis media, temporomandibular fracture, or history of ear surgery;(7)inappropriate condition for TEA administration due to skin disease or hemostatic disorder (prothrombin time international normalized ratio [PT INR] >2.0 or taking anticoagulant);(8)liver function abnormality (aspartate transaminase [AST] or alanine transaminase [ALT] levels greater than twofold the normal level);(9)renal function abnormality (serum creatinine or blood urea nitrogen [BUN] levels greater than twofold the normal level);(10)pregnancy or breastfeeding;(11)mental illness resulting in inability to comply with the clinical trial protocol; or(12)any other condition rendering the individual unsuitable for inclusion in the trial, as determined by the principle investigator (PI).

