### Sample size

2.7

The sample size was calculated on the basis of a previous similar study,^[29]^ as well as the advice of an expert group. With a 0.05 significance level, 90% power, 10% drop out rate, and 1:1 ratio, we determined, using the formula below, that the adequate sample size in each group is 28 participants (σ = 23.30 and *d* = 21.54): 

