### Statistical methods

2.10

The data will be corrected using the “last observation carried forward” method and then analyzed using the “intention-to-treat” analysis. The independent t-test or the Mann-Whitney U test for continuous variables and the Chi-square test or Fisher's exact test for categorical variables will be used to compare differences in general characteristics between the groups. As a primary outcome, changes in the FDI from baseline to the end of the 8-week treatment will be compared between the groups using the independent t-test. As secondary outcomes, changes in HB Grade, FNGE 2.0, SFGS, facial stiffness score, lip mobility score, and treatment satisfaction score will be also analyzed in the same way. All statistical analyses will be performed using PASW statistics 18, and the statistical significance level will be set at 0.05 (two-sided).

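### The FDI is collected twice before treatment, but the stated primary analysis is an unadjusted t-test on change from week 0 and gives the screening score no role: a conventional choice that gives up some precision

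*Protocol article*

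**What the plan says.** Section 2.6.1.1 (FDI) sets four measurement times: "The FDI score will be measured at a pre-trial screening and at weeks 0 (baseline), 4, and 8 (primary end point". Week 0 alone carries the label of baseline, and the endpoint follows from it: "The change from baseline at 8 weeks will be compared between the groups as the primary outcome".

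Section 2.10 (Statistical methods) fixes the test: "changes in the FDI from baseline to the end of the 8-week treatment will be compared between the groups using the independent t-test". It names no covariate for this comparison.

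Section 2.2 (Participants) explains why there is a screening measurement, since entry requires "Facial Disability Index (FDI) <80 on the social aspect and <70 on the physical aspect". Section 2.3 (Procedure) places eligibility screening before random allocation.

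Section 2.7 (Sample size) plans with "With a 0.05 significance level, 90% power, 10% drop out rate, and 1:1 ratio" and "σ = 23.30 and *d* = 21.54", and concludes that "the adequate sample size in each group is 28 participants". It does not say whether the SD belongs to the change or to the raw score.

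**The concern.** The FDI is self-reported, and a single administration carries measurement error. A change score subtracts the week-0 value with a weight of one, so all of that error passes into the outcome. The trial already holds a second pre-treatment score on the same instrument for every randomised patient, and the stated test has no place for it.

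What is at stake is precision, not validity. Allocation follows screening, so both arms are selected in the same way and the randomised comparison is unbiased with or without the screening score. In a trial of 56 patients, a tighter primary estimate that needs no further visit or question deserves consideration.

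**Working it through.** **Plan's own figure.** Inputs from 2.7 and 2.10: difference 21.54, SD 23.30, two-sided 0.05, power 90%, dropout 10%.

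- n per arm = 2 × [23.30 × (1.960 + 1.282) / 21.54]² = 24.59, rounded up to 25.
- With dropout: 25 / 0.9 = 27.8, rounded up to 28. The stated size reproduces.
- Power at 25 completers per arm is 90.5% by normal approximation and 89.3% by noncentral t. The plan meets its target, near enough, without the screening score.

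**Assumptions (not in the article).** Equal variances, scaled to 1. r is the correlation of each pre-treatment score with week 8, 0.4 to 0.6. c is the correlation between screening and week 0, 0.6 to 0.9. The central case is r = 0.5, c = 0.8.

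**Formulas.**

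- Change from week 0: 2 − 2r
- ANCOVA on week 0 only: 1 − r²
- ANCOVA on week 0 and screening: 1 − 2r²/(1 + c)

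| r | c | Change score | ANCOVA, week 0 | ANCOVA, both | Both v change score | Added by screening |
|---|---|---|---|---|---|---|
| 0.4 | 0.6 | 1.20 | 0.840 | 0.800 | −33% | 4.8% |
| 0.4 | 0.9 | 1.20 | 0.840 | 0.832 | −31% | 1.0% |
| 0.5 | 0.8 | 1.00 | 0.750 | 0.722 | −28% | 3.7% |
| 0.6 | 0.6 | 0.80 | 0.640 | 0.550 | −31% | 14.1% |
| 0.6 | 0.9 | 0.80 | 0.640 | 0.621 | −22% | 3.0% |

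ANCOVA on week 0 alone has (1 − r²)/(2 − 2r) = (1 + r)/2 of the change-score variance, a cut of 30%, 25% and 20% at r = 0.4, 0.5 and 0.6. That is most of the total in every row.

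**Cost of the second covariate.** With 50 completers, the residual degrees of freedom go from 47 to 46, a cost of about 1/47 = 2.1% of variance. In the central case the net gain from screening is about 3.7% − 2.1% = 1.6%.

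**On the power scale.** If 23.30 is the SD of the change, the central case at 25 per arm (normal approximation) gives:

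- t-test on change: 90.5%
- ANCOVA on week 0: SD 23.30 × √0.75 = 20.18, power 96.5%
- ANCOVA on both: SD 23.30 × √0.722 = 19.80, power 97.0%, before the cost in degrees of freedom

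**If screening predicts week 8 less well than week 0 does.** Write r_S and r_B for their correlations with week 8. Change from the mean of the two scores has variance 1 + (1 + c)/2 − (r_S + r_B), against 2 − 2r_B for change from week 0.

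- c = 0.8, r_S = 0.5, r_B = 0.6: 0.80 v 0.80, no gain from averaging.
- c = 0.8, r_S = 0.55, r_B = 0.7: 0.65 v 0.60, variance up 8%.

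For the covariate form, R² = (r_S² + r_B² − 2 r_S r_B c)/(1 − c²). The residual variance moves from 0.640 to 0.639 in the first case and stays at 0.510 in the second. Screening then adds nothing useful, and the loss is limited to the one degree of freedom.

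**Entry selection.** A simulation truncating the screening score at 0, 0.5 or 1 SD above its mean, with c from 0.7 to 0.9 and r of 0.5 or 0.7, gave residual variance ratios (both scores v week 0 only) of 0.865 to 0.986. The increment shrinks somewhat under selection but does not disappear.

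**The case against.** The case for leaving the plan alone is strong in several respects.

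- **No defect.** Sections 2.6.1.1 and 2.10 agree with each other, the last value before treatment is a standard baseline, and the screening score has a purpose in the entry cut-offs. This stands: nothing is contradictory or invalid.
- **The gain rests on assumed correlations.** The article gives none, and no interval between screening and week 0; the schedule figure is not shown. The Abstract times follow-up from screening, which hints at a short gap without proving it. A short gap pushes c towards 1 and the gain towards zero. This stands.
- **Most of the benefit is ordinary baseline adjustment.** This also stands, and the screening increment has to be reported separately from it.
- **The analysis plan is not shown.** It may add covariates. One can say only that the article gives the screening score no role, not that no planned analysis uses it. The article does, however, name both the baseline and the test, so the point concerns a stated choice and not an omitted detail.

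A reader might go further and infer that free precision is being thrown away, on the ground that averaging the two scores cuts change-score variance by 4–25%, or 10% centrally (0.90 v 1.00, about 6 of 56 patients). The documents do not support that. Those figures require screening and week 0 to predict week 8 equally well, and the unadjusted test to be kept. Where screening predicts less well, averaging can gain nothing or do harm. The screening score also appears to be the one selected on at entry, so averaging it in would lower the baseline and enlarge apparent within-group improvement through regression to the mean. A separate week-0 baseline limits this.

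**Conclusion.** The point holds as a small, optional efficiency improvement. A pre-treatment FDI score that the trial already collects has no role in the stated primary comparison, and that comparison adjusts for no baseline score at all.

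Under the assumed correlations, moving to a two-covariate ANCOVA removes about 22–33% of the change-score variance, 20–30% of it through week-0 FDI alone. Relative to ANCOVA on week 0, the screening score removes a further 1–14% before the cost in degrees of freedom, with a central net gain of between 1% and 2%. If the two visits are close together, or if screening predicts week 8 less well, it adds close to nothing and could cost about 2%. These figures depend on equal variances and, for the 1–14%, on equal prediction of week 8 by the two scores. The power figures also take 23.30 as the SD of the change.

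It should not be read as a flaw in the definition of baseline or as a shortfall in planned power.

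**What to change.** In 2.10, replace the t-test on the FDI change with a prespecified ANCOVA of week-8 FDI on treatment, with week-0 FDI and screening FDI as covariates, and fix this before unblinding. Week 0 stays as the baseline; do not redefine baseline as the mean of the two scores. If the two visits turn out by design to be close together, week-0 FDI alone as covariate captures nearly all of the gain.

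The cost is one sentence of analysis wording and one degree of freedom for each covariate. No visit, questionnaire or patient is added, and the sample size need not change.

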#### Secondary outcome measures

2.6.2

##### HB grade

2.6.2.1

The severity of facial palsy will be assessed using the HB Grade at weeks 0, 4, and 8. The Grade of I (normal function) to VI (total paralysis) is evaluated according to facial function at rest and with effort.^[25]^

##### FNGS 2.0

2.6.2.2

Facial nerve function will be assessed using the FNGS 2.0 at weeks 0, 4, and 8. The face is divided in four regions of the brow, eye, nasolabial fold, and oral commissure; then a score of1 (normal movement) to 6 (no movement) is provided for movement of each part. Additionally, secondary movement including synkinesis and contracture is scored from 0 (none) to 3 (disfiguring synkinesis; severe contracture). Summing the scores from each region and secondary movement produces a final score of 4 to 24, which is converted to a grade of I to VI (4, I; 5–9, II; 10–14, III; 15–19, IV; 20–23, IV; 24, VI).^[26]^

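### The FNGS 2.0 scoring rule contradicts itself: grade IV is printed for two bands and V for none, and the stated 4–24 range omits the 25–27 that its own items can reach

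*Protocol article*

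**What the plan says.** Section 2.6.2.2 (FNGS 2.0) of the protocol article sets out the scoring in three steps.

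- **Items.** "The face is divided in four regions of the brow, eye, nasolabial fold, and oral commissure", each scored 1 to 6 for movement. In addition, "secondary movement including synkinesis and contracture is scored from 0 (none) to 3 (disfiguring synkinesis; severe contracture").
- **Sum.** "Summing the scores from each region and secondary movement produces a final score of 4 to 24".
- **Grade.** The sum is the score "which is converted to a grade of I to VI". The first three bands are 4 for I, 5–9 for II and 10–14 for III; the last three are printed as "15–19, IV; 20–23, IV; 24, VI".

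The scale is assessed at weeks 0, 4 and 8. Section 2.10 (Statistical methods) states that "changes in HB Grade, FNGE 2.0, SFGS, facial stiffness score, lip mobility score, and treatment satisfaction score will be also analyzed in the same way", that is, by the independent t-test on change named for the primary outcome. It does not say whether the FNGS 2.0 variable is the total or the grade.

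**The concern.** Two statements in this section conflict with its own content. The scale is said to run from I to VI, yet the six bands carry only five different labels. The stated maximum of 24 is what the four regions give alone, although secondary movement is expressly included in the sum.

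FNGS 2.0 is a named secondary outcome whose change is compared between groups. A grade derived exactly as printed would hide some changes, exaggerate others and leave some patients without a value. Synkinesis and contracture, which the secondary-movement item scores, are among the typical sequelae listed in the Introduction and Discussion. The eligibility criteria limit the FDI but set no limit on facial grade, so the upper bands are not excluded by design.

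**Working it through.** **Inputs, all from section 2.6.2.2:** four regions, each 1–6; one secondary-movement item, 0–3; total = sum of both; stated range 4–24; six conversion bands.

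**1. Reproducing the stated range.**
- Regions only: 4 × 1 = 4 to 4 × 6 = 24. This gives the stated 4–24, but only by leaving out secondary movement.
- Regions plus secondary movement, as the text instructs: 4 × 1 + 0 = 4 to 4 × 6 + 3 = 27.
- If synkinesis and contracture were scored 0–3 separately: 4 to 24 + 3 + 3 = 30. The text describes a single 0–3 score, so this variant is not used.

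The section's own rule therefore gives 4–27, which is 24 possible totals.

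**2. Passing each total through the printed bands.**

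| Total | Printed grade | Number of totals |
|---|---|---|
| 4 | I | 1 |
| 5–9 | II | 5 |
| 10–14 | III | 5 |
| 15–19 | IV | 5 |
| 20–23 | IV | 4 |
| 24 | VI | 1 |
| 25–27 | none | 3 |

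Grade IV covers 5 + 4 = 9 totals (15–23). Grade V covers none.

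**3. What this does to a change in grade, if the map is used as printed.**
- 21 to 17, an improvement of 4 points: IV to IV, no change.
- 24 to 22, an improvement of 2 points: VI to IV, two grades.
- Any total of 25–27 at baseline or follow-up: no grade, so no change can be computed.

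**4. What is left after reading the second IV as V.** The six bands then carry I to VI, 21 to 17 becomes V to IV, and 24 to 22 becomes VI to V. Totals 25–27 still have no grade, and the stated range is still wrong.

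**5. How much of the scale lies above 24.** There are 6⁴ × 4 = 5,184 item combinations. A total above 24 needs:
- secondary movement 1 and a regional sum of 24: 1 combination;
- secondary movement 2 and a regional sum of 23 or 24: 4 + 1 = 5 combinations;
- secondary movement 3 and a regional sum of 22, 23 or 24: 10 + 4 + 1 = 15 combinations.

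Together 1 + 5 + 15 = 21, and 21 / 5,184 = 0.4%. This counts combinations, not patients. The protocol gives no score distribution from which to estimate the share of patients.

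**The case against.** The strongest reply is that nobody will be mis-scored. Six bands listed in order against six grades make the second IV an evident slip for V. The instrument is named and cited, and assessors would probably score from a CRF guide that is not shown. If the total is analysed, the grade map plays no part in the result. Totals above 24 need at least 22 of the 24 regional points, so synkinesis or contracture alone cannot produce them.

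Most of this stands, and it limits the consequence. It does not remove the inconsistency: the range is wrong under any reading that keeps secondary movement in the sum, and 25–27 stay ungraded after the label is repaired. Nor is this a detail left to a fuller document. The article states the scoring rule explicitly.

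A reader might infer three stronger points that the documents do not support:

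- **That the outcome will in fact be mis-scored.** This needs both literal use of the printed map and analysis of the grade. Section 2.10 settles neither, and nothing shows that the CRF carries the same error.
- **That a total of 24 is wrongly graded because some movement may remain.** Section 2.6.2.2 never defines FNGS grade VI as total paralysis. That description belongs to the separate HB Grade in section 2.6.2.1.
- **That the protocol must name the total as the analysed variable.** That choice may sit in a statistical analysis plan that is not shown.

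**Conclusion.** The point holds as an internal inconsistency in a scoring rule, and it is minor. On the protocol's own text, IV is assigned twice, V is never assigned, and the stated range of 4–24 should read 4–27 under the summing rule given. Three of the 24 possible totals are left without a grade.

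The effect on results depends on two things the article does not settle. If the printed map is applied and the grade is analysed, the distortions shown above follow, with ungraded values confined to near-complete palsies with secondary movement. If the total is analysed, only the stated range is wrong. That V was intended for 20–23 is a likely inference from six bands and six grades. The cited scale is not at hand to confirm it, nor to say which grade 25–27 should take.

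This is one of six listed secondary outcomes. The primary FDI comparison does not use it, and the sample-size calculation (σ = 23.30, d = 21.54) makes no use of the FNGS 2.0 conversion.

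**What to change.** Before any scoring, check section 2.6.2.2 against the cited scale and correct it so that:

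1. each of the six bands has a distinct grade, with 20–23 labelled V if the source confirms it;
2. the range of the summed score is stated as 4–27, matching the listed items;
3. totals of 25–27 are explicitly assigned to a grade, taken from the source.

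Then check that the CRF scoring guide, and any program that derives the grade, carry the same corrected map. The cost is a correction to the range and conversion wording in one section and a check of the scoring documents. No change to design, visits, sample size or primary analysis is needed.

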##### SFGS

2.6.2.3

Facial nerve function will also be assessed using the SFGS at weeks 0, 4, and 8. The SFGS consists of three parts: resting symmetry in three regions (eye, cheek, and mouth), symmetry of voluntary movement, and synkinesis in five expressions (forehead wrinkle, gentle eye closure, open mouth smile, snarl, and lip pucker). The scores from each part are weighted as follows: the resting symmetry score is multiplied by five, and the voluntary movement score is multiplied by four. Finally, the composite score is derived by subtracting the resting symmetry score and synkinesis score from the voluntary movement score.^[27]^

##### Facial stiffness score

2.6.2.4

The discomfort from facial stiffness will be assessed using the facial stiffness score at weeks 0, 4, and 8. Participants will be asked “To what extent is the discomfort in your life due to the stiffness of your face?” and rate their experienced discomfort on a six-point scale (0, no discomfort; 5, the worst discomfort they can imagine).

##### Lip mobility score

2.6.2.5

Lip mobility will be assessed using the lip-length index (LL-index) and snout index (S-index) at weeks 0, 4, and 8. The LL-index is calculated via the percentage change in lip length between grinning and resting. The S-index is calculated via the percentage change in lip length between puckering and resting. The lip length is measured by the intercommissural distance.^[28]^

##### Treatment satisfaction score

2.6.2.6

The satisfaction with the treatment will be assessed with three questions using a 10-point scale at week 8. Participants will be asked three questions regarding their satisfaction with the treatment, intent to receive further treatment in the future, and likelihood of recommending the treatment to other people. The participants will then score each question from 1 to 10 (1, very unsatisfied; 10, very satisfied).

### Sample size

2.7

The sample size was calculated on the basis of a previous similar study,^[29]^ as well as the advice of an expert group. With a 0.05 significance level, 90% power, 10% drop out rate, and 1:1 ratio, we determined, using the formula below, that the adequate sample size in each group is 28 participants (σ = 23.30 and *d* = 21.54): 

### Randomization and allocation concealment

2.8

A total 56 participants will be randomly allocated to the TEA group or the STEA group according to a block randomization procedure with a 1:1 ratio and block size of four. The randomization sequence will be generated by an independent statistician using the SAS (SAS Institute INC., Cary, NC, USA). Random codes will then be sealed in opaque envelopes and managed by a clinical research coordinator (CRC). After participation in the trial is confirmed via screening, the CRC will open the envelope and assign the participant to the allocated group according to a random code. To conceal the allocation until the end of the study, information with regard to the allocation will be recorded in a separate log and provided only to those researchers who are carrying out the intervention.

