**Method/Design::**

This is a patient-assessor blinded, randomized, sham-controlled trial with two parallel arms. Fifty-six patients aged 19–65 years, who have experienced sequelae of Bell's palsy for >3 months, will be recruited and screened using the eligibility criteria. After screening, they will be randomly allocated to a TEA group or a sham TEA (STEA) group. Both groups will receive TEA or STEA treatment on ten predefined acupoints once a week for 8 weeks. Additionally, both groups will receive the same acupuncture treatment twice a week for 8 weeks as a concurrent treatment. Changes in the Facial Disability Index over 8 weeks will be assessed as the primary outcome. Furthermore, the House-Brackmann Grade, Facial Nerve Grading System 2.0, Sunnybrook Facial Grading System, facial stiffness score, lip mobility score, and treatment satisfaction score will be measured and analyzed as secondary outcomes. All outcomes will be assessed at baseline and at 4 and 8 weeks after screening.

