## Introduction

1

Bell's palsy, also termed idiopathic facial paralysis, is one of the most common types of peripheral facial paralysis, and the specific cause is unknown.^[1]^ Weakness of the facial muscles is the main symptom of Bell's palsy, and is accompanied by posterior auricular pain, dry eyes, hyperlacrimation, taste disorder, dry mouth, or hyperacusis.^[2]^ The severity of the symptoms varies among patients, and approximately 29% of patients are known to experience sequelae; 12% experience mild sequelae, 13% experience moderate sequelae, and 4% experience severe sequelae.^[3]^

The sequelae of Bell's palsy including synkinesis, contracture, spasm, and crocodile tear syndrome typically occur approximately 3–6 months from the onset and persist for an extended period or permanently.^[4–6]^ Patients with sequelae of Bell's palsy exhibit facial asymmetry, deformities, and abnormal movements, and complain of subjective stiffness. In a society with a high level of interest in appearance, these symptoms severely degrade patient quality of life by causing psychological or social problems.^[7,8]^

Thread-embedding acupuncture (TEA) is a novel type of acupuncture that involves the insertion and embedding of absorbable foreign substances, such as catgut or polydioxanone, into acupoints using needles. Medical thread preserves the effect of traditional acupuncture for an extended period via the mechanical and chemical stimulations of the thread.^[9,10]^ TEA has been widely used for the treatment of musculoskeletal disease,^[11,12]^ obesity,^[13]^ and cosmetic purposes, particularly for reducing facial wrinkles and improving skin elasticity.^[14,15]^

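### Entry is open-ended from 3 months after diagnosis, but neither the allocation nor the primary test uses disease duration: a small possible loss of precision, not a bias

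*Protocol article*

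**What the plan says.** The Introduction (section 1) says that sequelae "typically occur approximately 3–6 months from the onset and persist for an extended period or permanently". Inclusion criterion 2 in section 2.2 asks for "a diagnosis of Bell's palsy made ≥3 months prior to screening" and sets no upper limit, so patients 4 months and 4 years after diagnosis both qualify on this criterion. The abstract (Method/Design) describes the population differently, as patients "who have experienced sequelae of Bell's palsy for >3 months".

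On allocation, section 2.8 says that "A total 56 participants will be randomly allocated to the TEA group or the STEA group according to a block randomization procedure". Blocks are of size four, allocated 1:1, and no stratification factor is named. Section 2.10 fixes the primary analysis as an independent t-test on the FDI change from baseline to week 8. It also compares general characteristics between the groups, but attaches no adjustment to that comparison.

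**The concern.** The primary outcome is a change over 8 weeks, so any spontaneous change in that period enters it directly. If patients in the emergence stage follow a different course from patients with established sequelae, disease duration is a prognostic factor. Baseline FDI need not capture it, because an early and a late patient can have the same score. With 28 patients per arm, the arms could differ noticeably in their share of early patients. The estimated difference would then carry part of that imbalance. Even without an imbalance, unexplained variation by stage would widen the confidence interval.

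**Working it through.** **Inputs from the protocol article.** Section 2.7: "With a 0.05 significance level, 90% power, 10% drop out rate, and 1:1 ratio", σ = 23.30, d = 21.54, and the result that "the adequate sample size in each group is 28 participants". Section 2.8: 1:1 allocation in blocks of four. Section 2.10: two-sided 0.05, independent t-test.

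**Inputs assumed, because the document gives neither.** The share of early-stage patients (3–6 months) is taken as 25–50%. The gap G between early and late patients in 8-week FDI change, regardless of arm, is taken as 10–15 points. Some simulations also use 0 or 20 points.

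**1. The plan's own sample size.** n = 2 × [σ(1.960 + 1.282)/d]² = 2 × [23.30 × 3.242/21.54]² = 24.6, rounded up to 25 per group. Dropout: 25/0.90 = 27.8, rounded up to 28. The stated figure reproduces.

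**2. Chance of imbalance.** With 56 patients and 28 per arm, the number of early-stage patients in one arm is hypergeometric. The probability that the arms differ by at least 6 early-stage patients (6/28 = 21 percentage points) is:
- 14 early-stage of 56 (25%): 0.121
- 28 early-stage of 56 (50%): 0.181

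**3. Shift caused by an imbalance of 6.** Shift = (6/28) × G.
- G = 10: 2.1 points
- G = 15: 3.2 points

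This is 10–15% of the planned 21.54. The standard error of the difference is 23.30 × √(2/28) = 6.23, so the shift is 0.34–0.52 standard errors. It can go in either direction.

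**4. Type I error.** Trials were simulated under the null with blocks of four, an early share of 30% or 50%, G = 0, 10 or 20, and total SD held at 23.30 (8,000 runs each). The planned t-test rejected in 4.6–5.2% of runs in every scenario, and a model adjusted for early/late stage also stayed at about 5%. Only within the subset of runs with an imbalance of at least 20 percentage points did the t-test's rejection rate rise, to about 7% (G = 10) and 11–12% (G = 20).

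**5. What adjustment buys.** The share of variance explained by stage is R² = G² p(1−p)/23.30². The interval narrows by about 1 − √(1−R²). Power is t-based, at 28 per arm and a true difference of 21.54.

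| G | Early share p | R² | Interval narrower by | Power, adjusted |
|---|---|---|---|---|
| 0 | any | 0 | 0% | 92.45% |
| 10 | 25% | 3.5% | 1.7% | 93.3% |
| 10 | 50% | 4.6% | 2.3% | 93.5% |
| 15 | 25% | 7.8% | 4.0% | 94.2% |
| 15 | 50% | 10.4% | 5.3% | 94.8% |

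The unadjusted t-test has 92.46% power (54 degrees of freedom). The covariate takes one degree of freedom, so the loss if duration is irrelevant is 0.01 percentage points.

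**The case against.** A reader might infer that chance imbalance in natural course could pass for a treatment effect, so that the trial's conclusion is unsafe. The document does not support that. Randomisation keeps the comparison unbiased on average, and the 5% error rate already allows for chance imbalance, as step 4 shows. Given an unlucky allocation, the shift is as likely to hide an effect as to mimic one.

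The premise is also an inference. The Introduction says when sequelae appear and that they last. It does not say that FDI drifts differently over 8 weeks by duration. Persistence points, if anything, to little spontaneous change, and section 2.2 requires patients to be impaired already (FDI below 80 on the social and below 70 on the physical aspect).

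A reader might also think that the problem exists however the entry window is read. It does not. Under the abstract's wording, patients have had sequelae for more than 3 months. As sequelae emerge at 3–6 months, most would be beyond 6 months from onset, and an early stratum would be nearly empty.

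Finally, unstratified blocks are an acceptable choice for a single-centre trial of 56, and a full protocol or analysis plan that is not shown could add a covariate.

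All of this stands and keeps the point minor. It does not remove it: under section 2.2 the duration range is open-ended, and the allocation and primary test, as the article fixes them, make no use of duration.

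**Conclusion.** The point holds as a minor matter of efficiency and robustness, and not as an error of validity. Under the assumed 10–15 point gap and 25–50% early share, the planned analysis gives up about 2–5% of interval width. In the 12–18% of allocations with an imbalance of 6 or more, the difference moves by at least 2.1–3.2 FDI points. Adjustment would raise power from about 92.5% to roughly 93–95%. If duration is not prognostic, the gain is nil. The gap and the early share are both assumptions, and the result depends further on the section 2.2 wording of the entry window being the operative one.

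**What to change.** 1. Reconcile the entry window first. The abstract counts time with sequelae and section 2.2 counts time since diagnosis, and the choice decides how many early-stage patients there can be.
2. Before unblinding, prespecify time since diagnosis as a covariate in the primary comparison, with a linear model for FDI change in place of the unadjusted t-test. The diagnosis date is already needed for inclusion criterion 2. That criterion does not establish the date of onset, so the term should be defined from diagnosis. A continuous term, or a cut-point suited to the reconciled window, is better than a fixed 3–6 month category that might be nearly empty. Adding the term only after an imbalance has been seen would be data-driven.
3. If recruitment has not begun, the envelope sequence may also be stratified by the same factor. If it has begun, keep the sequence and rely on the covariate.

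The cost is one model term and one degree of freedom. Stratifying would also need a second envelope series, and an incomplete last block of four could leave at most 2 patients of imbalance per stratum. The sample size of 28 per group does not change.
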